### Intervention

As part of this 6-month home-based intervention, each participant will be provided with a package designed to educate, motivate, and support improvement in nutrition and levels of physical activity through goal setting, based on the principles of Self-Determination Theory and Motivational Interviewing [15,16]. The program will empower individuals to self-manage and monitor their health behaviours and weight within their own environment (home). The approach will take particular care to emphasise the importance of regular self-weighing which is widely associated with greater weight loss (showing a 1 to 3 BMI unit advantage over individuals who do not self- weight frequently) [17]. In addition, frequent self-weighing is an important behavioural mediator in weight loss maintenance [18].

The intervention program is based on recent successful physical activity and nutrition programs (Physical Activity & Nutrition for Seniors [PANS] and the Perth Active Living Seniors [PALS]) specifically designed for older adults by the research team [19,20]. It will be adapted for the younger age group and the rural context. The intervention is safe, accessible, and low cost. Participants will commence it at a low level of physical activity, with aerobic, strength and flexibility components commensurate to the fitness level of each individual. The educational materials will provide illustrations and tips on how to perform exercises safely. The physical activity component will use accelerometers to measure programmed and incidental physical activity at baseline and post-test for the intervention group only, with graphical feedback provided to participants at baseline. The nutrition component will consist of suggested meal plans, recipes, and tips on healthy eating, encouraging a higher consumption of fruit/vegetables and fibre while reducing intake of saturated fat and sugar.

Research assistants will assist with the delivery of intervention resources and liaise with the participants to provide support and to monitor their goal setting. These assistants will receive a training manual including guidelines for diet and physical activity adherence, and will undergo training in Motivational Interviewing techniques [21]. They will make telephone contact with participants at weeks 3, 6, 12, 18 and 24 of the intervention. Additionally, follow-up emails will be used, and participants will have the option to contact the research assistant they have been allocated to.

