### Control group

The control group (n = 250) will be placed on a ‘waitlist’ to receive the intervention after they compete the post-test data collection. This group will not receive their risk scores; however will be informed they are eligible for the study after the first group have completed their program. Previous interventions have adopted this method of wait listing the control group [25,26].

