*Anthropometric measurements* will be undertaken by a certified anthropometrist at baseline and at 6-months post-test, following the International Society for the Advancement of Kinanthropometry guidelines. These include height and weight, body fat and muscle percentage, waist and hip circumference using a portable stadiometer, body composition scale, and tape measures, respectively [28,29]. *BMI* is promulgated as the most useful epidemiological measure of obesity along with *waist circumference*, while *waist-to-hip ratio* has been suggested as a better predictor of CVD mortality [33]. *Height* will be measured while the participant is barefoot to the nearest 0.1 cm with a portable stadiometer. *Weight* will be measured (wearing light clothing without shoes) using an electronic scale and recorded to the nearest 0.01 kg. *Waist and hip circumference* will be measured standing up at the level midway between the lowest rib margin and the iliac crest to the nearest 0.5 cm. *Hip* circumference will be measured at the largest level of the symphysis pubis and gluteus maximus. *Waist-to-hip ratio* will be calculated as waist circumference divided by hip circumference. *Blood pressure* will be measured by the trained research assistants using an Omron M5-1 electronic sphygmomanometer. A mean value will be recorded after three consecutive measurements (30).

A *self-reported questionnaire* will be completed by all participants at baseline (0-month) and post- test (6-months). This will include questions on demographics and lifestyle (smoking and alcohol drinking), the *International Physical Activity Questionnaire* (IPAQ) [13], and the *Fat & Fibre Barometer,* a valid and reliable instrument to assess dietary behavioural change [31]. The IPAQ Short Form has undergone reliability and validity testing in 12 countries. It has been used in many settings and was specifically designed for population-based physical activity studies.

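### Six-month blood pressure is assigned to the same staff role that coaches the intervention arm, so an unblinded coach can take the outcome reading in that arm only

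*Protocol article*

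**What the plan says.** **Who measures.** Under Outcome measures, in the text following Table 1, blood pressure "will be measured by the trained research assistants using an Omron M5-1 electronic sphygmomanometer". On the number of readings: "A mean value will be recorded after three consecutive measurements". The remaining physical measures go to a different role and "will be undertaken by a certified anthropometrist at baseline and at 6-months post-test". Blood is drawn by a phlebotomist and tested by a pathology laboratory.

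**Who coaches.** The Intervention section says: "Research assistants will assist with the delivery of intervention resources and liaise with the participants to provide support and to monitor their goal setting". These staff "will undergo training in Motivational Interviewing techniques". On contact: "They will make telephone contact with participants at weeks 3, 6, 12, 18 and 24 of the intervention", with follow-up emails in addition. There is a personal link as well: "participants will have the option to contact the research assistant they have been allocated to".

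**What controls receive.** Under Control group, this arm "will be placed on a ‘waitlist’ to receive the intervention after they compete the post-test data collection".

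**Where blood pressure enters.** It has its own row in Table 1. Through the systolic 130 mmHg or diastolic 85 mmHg criterion given under Recruitment, it is also one of the four additional components of metabolic syndrome, which is reclassified at 6 months.

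**The concern.** Of the physical and blood measures, blood pressure is the only one given to the role that also runs the intervention. By post-test, an intervention participant's assistant may have supported that person for six months. The assistant knows the allocation and has an interest in the result. A control has no such relationship with any assistant.

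An automatic monitor leaves the operator in charge of rest time, cuff placement, conversation, and whether a reading is repeated or accepted. A familiar operator may also lessen the participant's alerting response. If either effect differs between arms, it goes directly into the group-by-time contrast. Randomisation gives no protection, because the exposure arises after allocation. Analysis cannot remove it either if coaching and measuring coincide within one arm.

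At stake are the blood pressure comparison and, less directly, the blood pressure component of metabolic syndrome status.

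**Working it through.** **Step 1: which readings are exposed.** Blood pressure is first taken at screening stage 2. Random assignment follows only once eligibility is settled. Baseline readings therefore cannot depend on arm, and only the 6-month reading is exposed.

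**Step 2: whether the roles overlap.** The Outcome measures text refers to trained research assistants. The only research assistants whose training and duties the article describes are those in the Intervention section. No second group appears, and no sentence separates measuring from coaching. Overlap is therefore established for the role, not for named pairs of assistant and participant.

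**Step 3: inputs for the illustration.**
- From the protocol: 250 per arm with complete data and a 5% significance level. The recruitment figure behind this reproduces: 500 / 0.80 = 625.
- Assumed, because the article gives none of them: a two-sided test, a systolic SD of 15 mmHg (range 12 to 18), no true effect, and a differential measurement error b of 1 or 2 mmHg. An SD of 12 is also what baseline adjustment at a correlation of 0.6 would leave of 15: 15 × √(1 − 0.36) = 12.

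**Step 4: standard error of the group difference.** SE = SD × √(2/250). For SD 15, SE = 15 × 0.0894 = 1.34 mmHg.

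**Step 5: false-positive rate.** P = 1 − Φ(1.96 − b/SE) + Φ(−1.96 − b/SE).
- b = 0: 0.05.
- b = 1: b/SE = 0.745; P = 0.112 + 0.003, which is 0.116 before the parts are rounded.
- b = 2: b/SE = 1.491; P = 0.320, nearly all of it in the direction of the error.

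| SD (mmHg) | b = 1 mmHg | b = 2 mmHg |
|---|---|---|
| 12 | 0.154 | 0.462 |
| 15 | 0.116 | 0.320 |
| 18 | 0.095 | 0.237 |

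**Step 6: the systolic threshold.** With an assumed post-test mean of 132 mmHg and SD 15, the share at or above 130 is Φ(2/15) = 0.553. A 2 mmHg shift brings the mean to 130 and the share to 0.500, about 5 percentage points lower. This concerns systolic pressure alone. The criterion is also met by diastolic pressure or by treatment for hypertension, and the syndrome needs central obesity plus any two of four components. The effect on syndrome status would be smaller; it was not computed, because the article gives no joint distribution of the components.

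**The case against.** **Overlap of individuals is not stated.** A reader might infer that each coach measures his or her own participants. The article does not say so, and rostering may be set out in the full protocol. This limits the claim to what the text permits. It does not dispose of it, because the article does assign the measurement, and assigns it to the coaching role.

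**Familiarity may be slight.** Scheduled coaching is by telephone and email, and both arms attended the same central location for readings before randomisation. This stands, and it weakens the familiarity mechanism. Knowledge of allocation remains.

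**The device and the averaging protect.** They limit reading and rounding error and dilute any single discretionary reading. Averaging reduces random error but not a systematic difference between arms.

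**Direction is not shown.** A reader might infer a bias that can only favour the intervention. Conversation with a coach, or anxiety about performing for one, could raise readings instead. A favourable direction is the more likely, but it is an inference.

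**The magnitude depends on its assumption.** The 1 to 2 mmHg error has no source in the article. The calculation shows only that a trial of this size is sensitive to such an error if it occurs. This stands, and the figures are illustrative.

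**Blood pressure is not central.** It is not named in the hypothesis and does not drive the power calculation, while glucose and lipids lie outside the concern. This bears on the weight of the point, not on whether it holds.

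**Conclusion.** The point holds at role level. As written, the plan allows an intervention participant's post-test blood pressure to be taken by that participant's own unblinded coach, with no counterpart in the control arm. This follows from an assignment the article makes, not from a detail it leaves out.

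The direction probably favours the intervention and the size is unknown. If the differential error were 1 to 2 mmHg, with SD 15 mmHg, 250 per arm and no true effect, the false-positive rate for systolic pressure would be about 12% to 32% instead of 5%. Over SDs from 18 down to 12, it would be about 10% to 15% at 1 mmHg and 24% to 46% at 2 mmHg.

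Two stronger readings are not supported. The shift of about 5 percentage points across 130 mmHg cannot be read as a shift in metabolic syndrome status. Nor does the concern extend to waist circumference, which the article already gives to the certified anthropometrist. The sample size is unaffected. The change is worth making because it is cheap and the error could not be repaired after data collection.

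**What to change.** Amend the blood pressure sentence under Outcome measures so that the 6-month reading is taken by a research assistant who is not allocated to that participant, or by the certified anthropometrist if that person has no intervention role. The measurer should not be told the group where this is possible. The same measurement routine should apply in both arms, and all three device readings should be recorded along with their mean. If coaching and measuring staff are already separate, a sentence saying so settles the point.

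The cost is rostering at post-test visits. With the anthropometrist option there are also some extra minutes per visit, which matters because the Procedure section describes limited staffing, and the operator may differ from baseline, though equally in both arms. Some participants will reveal their group, so masking will be incomplete. No additional staff, procedure or participants are needed.

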## Methods

### Study design

This 6-month RCT will identify and recruit insufficiently active adults aged 50 to 69 with central obesity, residing in Albany, Western Australia, to participate in a home-based physical activity, nutrition, and healthy weight management intervention. Additional file 1: Figure S1 summarises the study design. A total of 500 participants with or at risk of metabolic syndrome will be recruited and randomised into intervention (n = 250) and wait-listed control (n = 250) groups. Data will be collected from both groups at baseline and 6 months to assess changes in outcome measures. Ethical approval of the study has been obtained from the Human Research Ethics Committee of Curtin University (HR149_2013). All participants will be informed of the research aims and objectives, and that confidentiality will be maintained throughout the study. Information and consent forms will be provided prior to entry into the RCT and participants will be free to withdraw from the program at any time.

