**Table 1 Tab1:** **Summary of outcome variables**

***Outcome variable***	***Measuring instrument***
Metabolic syndrome diagnosis/status	IDF criteria [5]
Glucose, triglyceride, cholesterol (total, LDL, HDL, non-HDL)	Blood samples [27]
Blood pressure	OMRON automatic BP monitor
Anthropometric measurements (BMI, waist circumference, waist-to-hip ratio, body fat and muscle percentage)	Body composition scale, stadiometer, measuring tape [28,29],
Physical activity (programmed, incidental)	ActiGraph GT3X Accelerometer [30]
Sedentary and physical activity behaviours	IPAQ [13]
Diet (fat, fibre, fruit, vegetable consumption)	Fat & Fibre Barometer [31]
Economic analysis	EQ-5D-3 L [32]

*Metabolic syndrome status* will be determined using the IDF criteria [5]. Participants satisfying the full criteria will be classified as having metabolic syndrome; whereas those with central obesity (waist circumference >94 cm men or >80 cm women [Europids, Sub-Saharan Africans, Eastern Mediterranean, Middle East]; >90 cm men or >80 cm women [South Asians, Chinese, Japanese]) plus any one of: raised triglyceride level (>1.7 mM, or treatment for this); reduced HDL-cholesterol (<1.03 mM in males and <1.29 mM in females, or treatment for this); will be classified as being at risk of metabolic syndrome. Post-test reclassification will determine changes to metabolic syndrome status after 6 months.

*Blood samples* will be taken by a phlebotomist at baseline and 6 months to measure a range of markers of cardiovascular disease risk and metabolic syndrome status. Fasting plasma glucose will be measured to assess insulin sensitivity. Fasting lipid levels will also be determined to assess lipid profile and CVD risk. The concentrations of triglycerides, total cholesterol and HDL cholesterol will be measured allowing determination of total-, LDL-, HDL-, and non-HDL-cholesterol levels [27]. All blood tests will be performed by Western Diagnostic Pathology.

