*Accelerometers (ActiGraph GTX3)* will be used to objectively measure physical activity in the intervention group [30]. Participants will be asked to wear an accelerometer for 7 days at baseline and at post-test. It will be worn at the left hip throughout waking hours, removed only for showering and swimming. Data collection will be set at one-minute intervals over the day. This information will be downloaded by researchers using the ActiLife 6 software. Data will be summarised into daily average counts (counts/mins/day) and activity durations (mins/day) in specific intensity levels (inactive, light, moderate, and vigorous). A calculated weight bearing Metabolic Equivalent Task score will be determined and compared within and between groups. This will allow monitoring of incidental activity and assessment of the effect of the intervention on physical activity levels. To ensure compliance, participants will receive instructions on the device and also complete a daily log [34].

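### Accelerometers are restricted to the intervention group, so the planned between-group comparison of accelerometer scores cannot be made and the one-arm change does not measure the intervention effect

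*Protocol article*

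**What the plan says.** Two places in the protocol article say who wears the device, and they agree. The Intervention section says: "The physical activity component will use accelerometers to measure programmed and incidental physical activity at baseline and post-test for the intervention group only". It adds that graphical feedback is given to participants at baseline. The accelerometer paragraph under Outcome measures says that the devices "will be used to objectively measure physical activity in the intervention group", with 7 days of wear at baseline and at post-test.

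The same Outcome measures paragraph then sets out two uses of the data. The first is a comparison: "A calculated weight bearing Metabolic Equivalent Task score will be determined and compared within and between groups". The second is an inference: "This will allow monitoring of incidental activity and assessment of the effect of the intervention on physical activity levels".

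Table 1 carries the accelerometer row, "Physical activity (programmed, incidental"), with no note that it applies to one arm. The Statistical analysis section plans to compare changes between the intervention and control groups and makes no exception for this outcome.

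**The concern.** A between-group comparison needs measurements in both groups, and the article provides accelerometer measurements in one. The planned comparison therefore cannot be carried out as described. The sentence about assessing the intervention's effect attaches a causal reading to data that can show only change over time in the treated arm.

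The accelerometer is the only objective measure of physical activity in Table 1. The other activity row is self-report by IPAQ. A reader of the article would reasonably expect an objective randomised comparison of activity, and the design as described does not supply one.

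**Working it through.** The check is one of consistency and data availability. The article states no figure for this comparison, so there is none to reproduce.

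**Step 1. Who contributes accelerometer data.**

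| Place in the protocol article | What it implies |
|---|---|
| Intervention | Intervention group only, baseline and post-test |
| Outcome measures, accelerometer paragraph, opening | Intervention group |
| Outcome measures, accelerometer paragraph, later sentences | Comparison between groups; assessment of the intervention's effect |
| Table 1 | Trial outcome, no arm restriction |
| Abstract, Methods/Design | Accelerometers listed among the intervention materials |
| Control group | 250 wait-listed; no device mentioned |

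No section gives a device to control participants. The planned counts with accelerometer data are therefore up to 250 in the intervention arm and 0 in the control arm.

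**Step 2. What the planned contrast requires.** Write I0 and I6 for the intervention means at baseline and 6 months, and C0 and C6 for the control means. The contrast between changes is

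(I6 − I0) − (C6 − C0),

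and, with a common standard deviation s of the change, its variance is s² × (1/nI + 1/nC). With nI = 250 and nC = 0, C0 and C6 do not exist and 1/nC is a division by zero. The contrast is undefined. The same holds for a simple post-test difference, I6 − C6, and for the group-by-time interaction, which is the term named under Sample size.

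**Step 3. What is left.** Only I6 − I0 can be estimated. It can be decomposed as

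I6 − I0 = programme effect + secular or seasonal change + change in reactivity to the device + natural fluctuation after selection.

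- Secular or seasonal change: the two measurements are six months apart. Screening is staggered (Procedure), which may spread start dates over the year, but nothing in the article ensures that this balances season.
- Reactivity: the same 7-day wear applies at both visits, so a constant reactivity would cancel. Only a difference in reactivity between visits remains.
- Natural fluctuation: participants are selected for less than 150 minutes of moderate activity per week (Recruitment). Selection does not use the accelerometer, so the device's measurement error plays no part in it. Real fluctuation in activity between screening, baseline and 6 months can still move the mean.

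The baseline graphical feedback is not in this list. It is part of the programme, so its influence belongs to the programme effect.

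The article gives no figures from which to size these terms, and without a control arm they cannot be subtracted.

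**Step 4. What is unaffected.** The self-reported questionnaire, which includes the IPAQ, is completed by all participants at baseline and 6 months. Both arms therefore have activity data from that instrument, and the contrast in Step 2 is defined for it.

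**The case against.** One could argue that control participants do wear the device, since Study design says: "Data will be collected from both groups at baseline and 6 months to assess changes in outcome measures". That sentence is general and names no instrument. It cannot override an explicit restriction to one group that is stated in the Intervention section and repeated in the accelerometer paragraph.

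One could also read the word groups as subgroups within the intervention arm, such as men and women, or take the score to be derived from the IPAQ. The article says neither. The sentence directly follows the summary of the accelerometer data, and the next one speaks of the intervention's effect.

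The stronger objection concerns weight, and it stands. The accelerometer is one of eight rows in Table 1 and is not named as primary. The hypothesis leads with insulin sensitivity and lipid profile. Sample size rests on the prevalence of physical activity participation without naming an instrument, and the IPAQ can supply that in both arms. Randomisation, sample size and the between-arm test of self-reported activity are untouched.

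A reader might infer that an uncontrolled change will be published as a randomised effect. The article does not say so. Its stated method compares changes between arms, and for this outcome that method yields no estimate at all rather than a biased one.

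**Conclusion.** The point holds, confined to the accelerometer outcome. The between-group comparison cannot be performed, because 0 of 250 planned controls contribute data. The one-arm change that remains should not be described as assessing the effect of the intervention. The direction and size of any bias in that change cannot be derived from the article, and none is claimed here.

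This should be corrected, but it does not threaten the trial. A reader might infer that the physical activity hypothesis as a whole is untestable or that the power calculation fails. The article does not support this, because the IPAQ is collected from everyone at both times.

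The conclusion assumes that the restriction to the intervention group means what it says. The study design figure in Additional file 1 was not available and is not relied on.

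**What to change.** Reconcile the Intervention section, Table 1 and the accelerometer paragraph under Outcome measures:

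1. In the accelerometer paragraph, remove the words that promise a comparison between groups, and keep the within-group comparison.
2. In the same paragraph, remove the claim that these data assess the intervention's effect on physical activity.
3. In Table 1 and in that paragraph, label the accelerometer as an intervention-arm measure, used for descriptive pre-post summaries and for feedback.
4. State that the randomised between-group comparison of physical activity uses the self-reported IPAQ, which is already collected from all participants at both times.

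This changes wording only and needs no further data. The price is a weaker claim, since the trial then has no objective randomised activity result. If the investigators want one, control participants would have to wear the same devices for 7 days at both visits. That brings device logistics, and it must be arranged before the controls' baseline visit, because a missed baseline reading cannot be recovered.
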